# Effect of inspiratory muscle training on hypoxemia in obese patients undergoing painless gastroscopy: protocol for a single-center, double-blind, randomized controlled trial

**DOI:** 10.3389/fmed.2023.1269486

**Published:** 2023-09-14

**Keywords:** inspiratory muscle training, obesity, hypoxemia, painless gastroscopy, randomized controlled trial, the Pittsburgh Sleep Quality Index

## Abstract

**Introduction:**

Obese patients who undergo painless gastroscopy are particularly prone to suffer from upper airway obstruction, respiratory depression, and subsequent hypoxemia. Despite adequate preoxygenation, the incidence of hypoxemia remains high. Recently, inspiratory muscle training (IMT) has been considered to be a promising strategy to increase respiratory muscle strength and endurance with the attendant improvement of pulmonary function. However, it remains unclear whether IMT is associated with a lower rate of hypoxemia in obese patients during this sedative procedure. This study aims to investigate the effectiveness of IMT used in obese patients who are scheduled for selective painless gastroscopy.

**Methods and analysis:**

This prospective, randomized controlled trial (RCT) will enroll 232 obese patients with a body mass index (BMI) of 35–39.9 kg·m^−2^ who undergo painless gastroscopy at the First Affiliated Hospital of Xiamen University. Subjects will be randomly assigned to two groups with a 1:1 ratio. Participants in both groups will receive IMT for 4 weeks prior to gastroscopy. The intervention group will receive IMT with a load of 30% of the maximal inspiratory pressure (Pi(max)) in the first week, with an increase of 10% per week since the following week, while the counterparts in the control group will not receive any load during the 4-week IMT. The primary outcome is the incidence of hypoxemia during painless gastroscopy. Secondary outcomes include the need for airway maneuvers, blood pressure changes, sleep quality assessment, pro-inflammatory cytokines levels, and monitoring of adverse events.

**Discussions:**

The outcomes of this study will offer invaluable guidance for the clinical implementation of IMT as a potential non-invasive preventive measure. Additionally, it stands to enrich our comprehension of anesthesia management and airway-related challenges in obese patients undergoing procedural sedation, which we anticipate will further contribute to addressing the turnaround concerns within high-volume, swiftly paced ambulatory endoscopy centers.

**Ethics and dissemination:**

This study has been approved by the Ethics Committee of the First Affiliated Hospital of Xiamen University (2022, No.091). The results will be submitted for publication in peer-reviewed journals.

**Trial registration number:**

China Clinical Trial Center (ChiCTR2200067041).

## Introduction

With the continuous improvement of living standards, an increasing number of patients are seeking safe and comfortable endoscopes to alleviate anxiety, pain, and discomfort during examinations. Hypoxemia is a common occurrence during upper gastrointestinal endoscopy, with an approximate incidence of 15% (1). It is important to note that more than one-third of the world’s population is overweight or obese patients (2), leading to a high incidence of hypoxemia, reaching 30.8%, during painless gastroscopy (3). Obesity is associated with a higher prevalence of hypoxemia due to factors such as mechanical compression of the chest wall, poor lung function, limited oxygen reserve capacity, increased oxygen consumption (4, 5), upper airway obstruction (6–8), and respiratory depression during procedural sedation (9). It is crucial to acknowledge that hypoxemia significantly contributes to various complications including brain damage, coronary ischemia, and tachycardia (9, 10). Therefore, optimal airway management to avoid hypoxemia is urgently needed for specific high-risk populations treated in high-volume, fast-paced, outpatient endoscopy centers.

Currently, there is no consensus on how to enhance oxygenation for obese patients during painless endoscopy procedures. The use of opioids and sedatives in such cases is closely linked to respiratory depression and airway blockage. However, recent evidence suggests that the combination of opioid-free analgesia esketamine and remimazolam can help mitigate sedation-induced respiratory depression and lower the occurrence of severe hypoxemia in obese patients undergoing painless gastrointestinal endoscopy (9). The existing strategies, including nasal cannula oxygenation supply, Wei nasal jet tubes, or supraglottic pulsatile jet oxygenation (8, 11), have provided partial prevention of airway collapse or obstruction (6). It is important to acknowledge that these approaches mainly target the upper airway rather than the smaller airways, leading to limited tolerance during the recovery phase and potentially unsuitability for high-risk hypoxemia patients. While the efficacy and safety of high-flow nasal cannula (HFNC) as a promising alternative for improving oxygenation in obese individuals have been established (2, 12–14), the practical implementation of HFNC in less developed regions remains unfeasible due to the requirement for specialized equipment, trained personnel, and the associated high costs (9). Therefore, it is crucial to identify an effective, practical, and non-invasive method to improve hypoxemia during painless gastroscopy for obese patients.

In recent times, the global impact of the coronavirus disease (COVID-19) has sparked considerable interest in inspiratory muscle training (IMT) as a fitness program, with the potential to alleviate symptoms of breathlessness, anxiety, and fatigue (15–17). IMT involves resistance-loaded muscle training using a small breathing device and is widely utilized in pulmonary rehabilitation settings (18). Its purpose is to enhance the performance of both primary and accessory respiratory muscles, improve physiological reserve, preserve the patency of smaller airways, increase maximal voluntary ventilation, and facilitate lung expansion (4, 15, 17, 19, 20). Several pieces of evidence have indicated that preoperative IMT can increase maximum inspiratory pressure (Pi(max)), decrease postoperative pulmonary complications, improve exercise endurance, and shorten hospital stays (21–23). Short-term IMT has shown significant improvements not only in oxygenation for patients undergoing lung cancer surgery (16) but also in reducing breathlessness and enhancing respiratory muscle function in individuals with long COVID-19 or obesity (24–26). In the intensive care unit, IMT has proven to be an effective method for reversing inspiratory muscle weakness, facilitating early weaning from mechanical ventilation, and enhancing weaning outcomes (27, 28) by increasing diaphragm thickness, an independent predictor of adverse outcomes measured by ultrasonography (29–31). Additionally, IMT has demonstrated positive effects on athletes, improving athletic performance and reducing inspiratory muscle fatigue (32). Presently, there are no reports of IMT being used to improve oxygenation during procedural sedation. However, we speculate that IMT could be a potential, practical, and non-invasive physical activity strategy to reduce the incidence of hypoxemia in obese patients undergoing procedural sedation.

To the best of our knowledge, this study represents the first attempt to assess the effect of IMT in reducing the incidence of hypoxemia during painless gastroscopy in obese individuals. For medical ethics and safety, this randomized controlled trial (RCT) will include 232 obese patients with a BMI ranging from 35 to 39.9 kg·m^−2^, all of whom are scheduled to undergo a 4-week IMT program prior to painless gastroscopy. Additionally, we aim to compare the impact of different IMT protocols on the requirement for airway maneuvers, blood pressure, sleep quality, pro-inflammatory cytokine levels, and any potential adverse events that may arise.

## Methods and analysis

### Study design

This study is a single-center, double-blinded RCT scheduled to take place at the Endoscopy Center of the First Affiliated Hospital of Xiamen University. Participants will be assigned randomly to either the intervention or control group in a 1:1 ratio. The protocol adheres to the Standard Protocol Items: Recommendations for Interventional Trials guidelines (33) and will be conducted following the study’s flow chart (Figure 1).

**Figure 1 fig1:**
[figure not shown]
Flow chart of the study. BMI, body mass index; ASA, American Society of Anesthesiologists; COVID-19, the coronavirus disease.

To begin, participants will undergo IMT for 4 weeks before the gastroscopy procedure. In the intervention group, IMT will be administered with a load of 30% of the Pi(max) during the first week. Starting from the second week, the load will be increased by 10% each subsequent week. Conversely, the control group will not receive any load during the 4-week IMT period.

Subsequently, all patients will receive the same sedation strategy comprising remimazolam tosilate and esketamine. The gastroscopy procedure will be performed under a stable level of sedation. After the examination, patients will be transferred to the post-anesthesia care unit (PACU) and discharged once their modified Aldrete score reaches 9.

Lastly, all data will be collected as per the schedule outlined in Table 1.

**Table 1 tab1:** The schedule of enrollment, interventions, and assessments.

Study period	Screening	Allocation	IMT		Anesthesia and examination		PACU	Follow-up		
		T1		T2		T3		T4	T5	T6
**Enrollment**										
Inclusion criteria	X									
Exclusion criteria	X									
Informed consent	X									
Randomization	X									
Demographics data	X									
Physical examination data	X									
Allergy history	X									
Comorbidities	X									
**Interventions**										
The intervention group			[figure not shown]							
The control group			[figure not shown]							
**Assessments**										
**Clinical monitoring**										
(1) Vital signs	X	X		X	X		X			
(2) Pi(max)		X								
(3) MOAA/S				X	X					
(4) BIS				X	X					
**Outcome assessment**										
(1) The incidence of hypoxemia					X					
(2) The need for airway maneuvers					X					
(3) Blood pressure		X		X	X		X			
(4) Sleep quality		X		X				X	X	X
(5) Pro-inflammatory cytokines levels		X		X		X				
(6) Adverse events					X		X			
**Requirement for vasoactive agents**					X		X			
**Need for rescue sedatives**					X		X			

IMT, inspiratory muscle training; PACU, post-anesthesia care unit; Pi(max), maximum inspiratory pressure; MOAA/S, Modified Observer’s Assessment of Alertness and Sedation; BIS, bispectral index; T1, 1 day before IMT; T2, immediately prior to anesthesia; T3, at the conclusion of the gastroscopy; T4, on the night of the gastroscopy; T5, 1 week after the gastroscopy; T6, 4 weeks after the gastroscopy.

### Participant enrollment

Between September 2023 and August 2024, potential subjects for this study will be recruited from the outpatient clinic of the Department of Anesthesiology. This clinic handles a monthly volume of over 2000 patients undergoing painless gastroscopy, and the prevalence of obesity in this population exceeds 1 percent. Out of the eligible candidates, a total of 232 patients will be enrolled. Before enrollment, these individuals will receive comprehensive information regarding the study’s purpose, procedures, considerations, potential benefits and risks, as well as any associated costs. They will be fully informed and have the opportunity to provide voluntary consent to participate. Both the subjects and their authorized representatives will be responsible for maintaining the confidentiality of the received protocol. Written informed consent will be obtained from all subjects prior to their enrollment. Participants will have the freedom to withdraw from the study at any point without incurring any liability, and such withdrawal will not impact their subsequent gastroscopy procedures.

### Participants’ inclusion and exclusion criteria

All potential subjects will undergo a screening process based on the defined inclusion and exclusion criteria. If a subject meets the following shedding criteria, they will be excluded from this study.

### Inclusion criteria

Patients with a body mass index (BMI) ranging from 35 to 39.9 kg·m^−2^.Patients classified as American Society of Anesthesiologists (ASA) Class I or II.Patients between the ages of 18 and 50 years.

### Exclusion criteria

Patients classified as ASA Class III or higher.Patients with a known history of allergy to remimazolam tosilate or esketamine.Pregnant or lactating patients.Patients with mental disorders.Patients with a full stomach.Patients scheduled for complicated or therapeutic gastroscopy.Patients who are participating in other clinical trials.Patients with known difficult airways, such as limited neck movement or limited mouth opening.Patients who have been affected by COVID-19 within the past 7 weeks.Patients who are currently taking antihypertensive medications.

### Shedding criteria

Patients or their authorized representatives request to withdraw at any stage of the study.Severe complications arise during the examination, necessitating prolonged examination or emergency surgery.Severe hypoxemia occurs during the study, requiring endotracheal intubation.

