### Intervention

This study aims to assess the impact of IMT on enhancing oxygenation levels during painless gastroscopy in individuals with a BMI of 35–39.9 kg·m^−2^. Upon identifying the participants, an intervention delivery schedule will be established. Before undergoing gastroscopy, participants will follow a 4-week IMT intervention protocol based on their assigned group. The timeline for enrollment, interventions, and assessments is outlined in detail in Table 1. All data will be collected according to the participant’s specific timeline, which includes the following time points: T1: 1 day before IMT, T2: immediately prior to anesthesia, T3: at the conclusion of the gastroscopy, T4: on the night of the gastroscopy, T5: 1 week after the gastroscopy, and T6: 4 weeks after the gastroscopy.

For participants assigned to the intervention group, a research assistant will measure their Pi(max) using the IMT device (POWER^®^breathe, Tianrui, Jiangsu). During the measurement process, patients will be seated and wear a nasal clip. They will exhale slowly and completely, followed by inhaling with maximum force and holding it for at least 1.5 s. The inspiratory pressure at this point will be recorded. This process will be repeated three times, and the average of the recorded inspiratory pressures will be considered as the Pi(max).

POWER^®^breathe follows a standard practice of conducting 30 inspiratory breaths twice a day (20). The intervention group will undergo IMT using a load equivalent to 30% of their Pi(max) during the first week. Starting the following week, the load will be increased by 10% each week for a total of three adjustments. On the other hand, participants in the control group will not receive any load during the 4-week IMT. It is important to note that participants will not be informed about their assignment to either the intervention or control group.

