### Primary outcomes

The primary outcome of this study is the incidence of hypoxemia during painless gastroscopy. Hypoxemia will be defined as a SpO_2_ level below 90%.

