### Statistical analysis

An independent biostatistician, not involved in our trial, will analyze all the data using optimal software. We will use the Last Observation Carried Forward (LOCF) imputation method to handle missing data. However, this study will not include interim analyses.

Continuous variables will be assessed using either the *t*-test or Wilcoxon rank test, depending on the nature of the data. For the analysis of counting data, the chi-square test or Fisher’s exact test will be employed for comparison. Statistical significance will be defined as *p*<0.05.

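### The withdrawal rule excludes randomised patients at any stage without separating stopping training or follow-up from withdrawing consent to data use, and LOCF cannot fill the primary outcome they leave missing

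*Protocol article*

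**What the plan says.** All locations are in the protocol article.

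- **Participants' inclusion and exclusion criteria** sets the consequence: "If a subject meets the following shedding criteria, they will be excluded from this study".
- **Shedding criteria** lists as its first item: "Patients or their authorized representatives request to withdraw at any stage of the study". The other two items are events that arise during the procedure or study (severe complications, and severe hypoxemia requiring intubation).
- **Participant enrollment** treats withdrawal as the participant's free right and adds that "such withdrawal will not impact their subsequent gastroscopy procedures".
- **Table 1** places randomisation at screening, before the 4 weeks of training. Sleep follow-up runs to T6, 4 weeks after the gastroscopy.
- **Intervention** describes the two arms: "The intervention group will undergo IMT using a load equivalent to 30% of their Pi(max) during the first week", with weekly increases after that, while "participants in the control group will not receive any load during the 4-week IMT". It also says that "participants will not be informed about their assignment to either the intervention or control group".
- **Primary outcomes**: "The primary outcome of this study is the incidence of hypoxemia during painless gastroscopy". Table 1 assesses it only in the anesthesia and examination period.
- **Sample size** allows for 10% dropout, not split by arm or reason.
- **Statistical analysis**: "We will use the Last Observation Carried Forward (LOCF) imputation method to handle missing data".

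**The concern.** The rule acts after randomisation and attaches one consequence, exclusion, to any request to withdraw, whatever the patient wants to stop and whenever they ask. Three situations are not told apart: ending the training but agreeing to be observed at the gastroscopy, ending the questionnaires after the gastroscopy, and withdrawing consent to the use of data. Only the third obliges the trial to give up an outcome.

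Two things are at stake. First, primary outcomes that exist or could be obtained with consent may be discarded. Second, if the patients who leave differ in risk from those who stay, and the net effect differs between arms, the analysed groups are no longer comparable. The arms ask for different effort, so this is plausible. The fallback does not help: hypoxemia is assessed once, and a patient without that assessment has no previous value.

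**Working it through.** **Step 1: reproduce the plan's own figure.** Inputs from the Sample size section are 40% versus 20%, 90% power and type I error 0.05 (taken as two-sided, which the article does not state). Unpooled formula: n = (0.40×0.60 + 0.20×0.80) × (1.960 + 1.282)² / 0.20² = 0.40 × 10.507 / 0.04 = 105.07 per group, which agrees with the stated 105. Then 105 × 1.1 = 115.5, rounded to 116 per group and 232 in total. (Dividing by 0.9 gives 117 per group.) The sample size is therefore not the issue. The plan expects to lose about 10% of 232, or some 23 patients.

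**Step 2: what the exclusion covers.** Withdrawal is allowed at any stage and follow-up ends at T6. A patient who completes the gastroscopy and declines the 1-week or 4-week questionnaire by asking to withdraw meets the criterion after the primary outcome has been recorded. The article does not say whether that outcome is kept. Two features make removal from the analysis the natural reading. The other shedding items can arise during the procedure itself, when little remains to be excluded from except the analysis. The sample size is also inflated for dropout.

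**Step 3: LOCF.** It needs an earlier measurement of the same variable. PSQI, blood pressure and cytokines have baseline values. Hypoxemia during gastroscopy has none, so the stated method is undefined for the primary outcome.

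**Step 4: how large a bias could be.** The documents give no withdrawal rate by arm and no risk among leavers, so these are assumptions. Set no true effect, overall risk 40% in both arms and 116 randomised per arm. With a proportion d leaving at risk r, the analysed rate is (0.40 − d×r)/(1 − d). Type I error is the exact rejection probability of the two-sided chi-square test on the remaining patients.

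| Leaving, loaded vs control | Leavers' risk (both arms) | Analysed rates | Spurious difference | Type I error |
|---|---|---|---|---|
| 10% vs 10% | 60% | 37.8% vs 37.8% | 0 | about 5.2% |
| 15% vs 5% | 40% | 40% vs 40% | 0 | about 5.0% |
| 12% vs 8% | 60% | 37.3% vs 38.3% | 1.0 point | about 5.6% |
| 15% vs 5% | 50% | 38.2% vs 39.5% | 1.2 points | about 5.5% |
| 15% vs 5% | 60% | 36.5% vs 38.9% | 2.5 points | about 6.7% |
| 15% vs 5% | 20% | 43.5% vs 41.1% | 2.5 points against training | about 6.4% |
| 20% vs 0% | 60% | 35% vs 40% | 5 points | about 11.6% |

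Worked row: (0.40 − 0.15×0.60)/0.85 = 0.31/0.85 = 36.5%, and (0.40 − 0.05×0.60)/0.95 = 0.37/0.95 = 38.9%.

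If only the loaded arm's leavers are at raised risk (control leavers at 40%), 10% leaving each arm gives 2.2 points at 60% risk and 4.4 points at 80%. With 15% vs 5% leaving, the figures are 3.5 and 7.1 points.

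**Step 5: cost of keeping patients who stop training.** If 10% of the loaded arm have the control risk, its rate is 0.9×20% + 0.1×40% = 22%. At 116 per arm, 40% versus 22% has power of about 85%, against about 92% for 40% versus 20%.

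**The case against.** The strongest reply is that the criterion covers only people who ask to leave, which is a consent right and not an exclusion imposed by the investigator. Several parts of that case stand.

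- A reader might infer that the protocol treats stopping training as withdrawal and removes both groups. It does not say so. A patient who misses sessions without asking to leave meets no shedding criterion. The defect is that the line is not drawn.
- A reader might infer that, because the gastroscopy goes ahead, the outcome is available for most leavers. The documents do not support this. The sedation and monitoring are described for study subjects, and the Strengths section says that common practice in China is a different regimen. Someone who has fully left need not receive the trial sedation, and data cannot simply be collected for the trial once consent has ended.
- A reader might infer that withdrawal will depend on arm and inflate the type I error. Participants are not told their group, both arms follow a 4-week programme, and both receive real-time video instruction. Unequal withdrawal alone gives no bias when leavers have the same risk as stayers. The direction can also reverse.
- Larger error rates follow if LOCF is taken to score leavers as having no hypoxemia. The protocol does not say that.
- Exclusion from the analysis is inferred from exclusion from the study. The article names no analysis set, and a fuller document may do so.

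The reply does not remove the rule itself. The article states a consequence for any withdrawal at any stage, including after the outcome is recorded, and names a method that cannot work for the primary outcome.

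**Conclusion.** The point holds as a defect in a stated rule. Exclusion on any withdrawal request, at any stage, makes no distinction between stopping training or follow-up and withdrawing consent to data use. On a literal reading it can discard a primary outcome already in hand. LOCF is undefined for that outcome; this follows from the schedule and needs no assumption.

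The bias is a possibility and has not been shown. Under assumed inputs it runs from none (balanced withdrawal at equal risk, or leavers with the same risk as stayers) through 1 to 2.5 points for moderate imbalance, to 5 to 7 points only when the imbalance is extreme or the raised risk is large and confined to the loaded arm's leavers. These figures also assume that leavers are omitted from the analysis, which is the natural reading but not an explicit statement. The change is worth making before recruitment because outcomes not recorded on the day cannot be recovered.

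**What to change.** Reword the criterion and the matching consent text to state:

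1. Stopping training, or declining later questionnaires, is not a shedding event. With the patient's continued consent, SpO2 and airway maneuvers are recorded at the study gastroscopy.
2. Data collected before a withdrawal are kept and used unless the patient withdraws consent to their use.
3. The primary analysis includes every randomised patient with an observed gastroscopy outcome, in the randomised group. For those without one, a best/worst-case sensitivity analysis replaces LOCF.

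The cost is redrafting, with no added visit for patients who remain under study observation. Retaining patients who stopped training may dilute the effect, to about 85% power in the case worked above. The estimate would then describe the effect of assigning the loaded training.

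Best/worst-case bounds are wide. With 10% missing per arm and 40% versus 20% among those observed, the loaded arm's rate lies between 0.9×20% = 18% and 18% + 10% = 28%. The control rate lies between 0.9×40% = 36% and 46%. The difference therefore ranges from 36 − 28 = 8 to 46 − 18 = 28 points. This is a further reason to keep missing outcomes few through items 1 and 2.

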If any involuntary movements, such as coughing, raising the head, or body shifting, are observed in a patient, an immediate infusion of remimazolam tosilate at a dose of 0.05 mg·kg^−1^ will be administered. If such movements persist after 1 min, a reapplication of remimazolam tosilate may be necessary. After the examination, all patients will be transferred to the PACU for recovery.

In cases where the heart rate is less than 45 beats per minute or exceeds 100 beats per minute, Atropine at a dose of 0.5 mg or Esmolol at a dose of 1 mg·kg^−1^ will be administered separately to address the situation. Similarly, if the mean arterial pressure deviates by more than 20% from the baseline, Phenylephrine at a dose of 40 μg or Urapidil hydrochloride at a dose of 12 mg will be promptly administered accordingly.

If a patient’s SpO_2_ falls below 90%, the experienced anesthesiologist must differentiate between respiratory obstruction and respiratory depression (34). For respiratory obstruction, the anesthesiologist will apply jaw-lift. On the other hand, respiratory depression will be managed using appropriate measures such as positive-pressure ventilation using a bag-mask.

If deemed necessary, flumazenil will be employed to counteract the effects of remimazolam tosilate. However, in the event of severe hypoxemia and if the aforementioned methods prove ineffective, the anesthesiologist will promptly administer either a laryngeal mask or perform endotracheal intubation to ensure adequate airway management.

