### Secondary outcomes

The secondary outcomes encompass several measures, including the need for airway maneuvers, blood pressure changes, sleep quality assessment, pro-inflammatory cytokine levels, and monitoring of adverse events such as bradycardia, tachycardia, nausea, and vomiting.

For this study, airway maneuvers will be defined as jaw-lift, positive-pressure ventilation with a bag-mask, insertion of a laryngeal mask, or endotracheal intubation.

Blood pressure will be measured at different time points: before IMT, prior to anesthesia, during the examination, and in the PACU.

Sleep quality and duration will be assessed using the Pittsburgh Sleep Quality Index (PSQI), a 19-item questionnaire (Table 3), at T1, T2, T4, T5, and T6. A patient scoring greater than 5 on the PSQI will be classified as a poor sleeper (35).

**Table 3 tab3:** The questionnaire of Pittsburgh Sleep Quality Index.

1. During the past month, when have you usually gone to bed?				
2. During the past month, how long (in minutes) has it taken you to fall asleep each night?	≤15 min (0)	16 ~ 30 min (1)	31 ~ 60 min (2)	>60 min (3)
3. During the past month, when have you usually gotten up in the morning?				
4. During the past month, how many hours of actual sleep did you get that night? (This may be different than the number of hours you spend in bed)	>7 h (0)	6 ~ 7 h (1)	5 ~ 6 h (2)	<5 h (3)
5. During the past month, how often have you had trouble sleeping because you…	Not during the past month (0)	Less than once a week (1)	Once or twice a week (2)	Three or more times a week (3)
a. Cannot get to sleep within 30 min	(0)	(1)	(2)	(3)
b. Wake up in the middle of the night or early morning	(0)	(1)	(2)	(3)
c. Have to get up to use the bathroom	(0)	(1)	(2)	(3)
d. Cannot breathe comfortably	(0)	(1)	(2)	(3)
e. Cough or snore loudly	(0)	(1)	(2)	(3)
f. Feel too cold	(0)	(1)	(2)	(3)
g. Feel too hot	(0)	(1)	(2)	(3)
h. Have bad dreams	(0)	(1)	(2)	(3)
i. Have pain	(0)	(1)	(2)	(3)
j. Other reason(s), please describe, including how often you have had trouble sleeping because of this reason(s)	(0)	(1)	(2)	(3)
6. During the past month, how often have you taken medicine (prescribed or “over the counter”) to help you sleep?	Not during the past month (0)	Less than once a week (1)	Once or twice a week (2)	Three or more times a week (3)

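### The shedding criteria exclude, after randomisation, patients intubated for severe hypoxemia, who are themselves primary-outcome events; the resulting bias is of unknown size and direction

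*Protocol article*

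**What the plan says.** Four places in the protocol article bear on this.

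- **Participants' inclusion and exclusion criteria** sets the consequence of shedding: "If a subject meets the following shedding criteria, they will be excluded from this study".
- **Shedding criteria** lists three grounds. The first is withdrawal by the patient or a representative. The second is "Severe complications arise during the examination, necessitating prolonged examination or emergency surgery". The third is "Severe hypoxemia occurs during the study, requiring endotracheal intubation".
- **Primary outcomes**: "The primary outcome of this study is the incidence of hypoxemia during painless gastroscopy", with hypoxemia defined as SpO2 below 90%.
- **Secondary outcomes**: "airway maneuvers will be defined as jaw-lift, positive-pressure ventilation with a bag-mask, insertion of a laryngeal mask, or endotracheal intubation".

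The section on monitoring and anesthesia makes intubation part of the rescue pathway. For severe hypoxemia that other measures have not corrected, "the anesthesiologist will promptly administer either a laryngeal mask or perform endotracheal intubation to ensure adequate airway management".

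Statistical analysis names LOCF for missing data. It does not say how shed patients are handled.

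**The concern.** Table 1 places randomisation at screening, before the four weeks of training, whereas the second and third shedding grounds arise later, the second by its terms during the examination itself. They are therefore exclusions after randomisation and not screening rules.

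The third ground is the more serious. A patient intubated for severe hypoxemia during the procedure has, by definition, had SpO2 below 90%, so the patient is removed because the primary event occurred. That conditions the randomised comparison on its own outcome. It also means that the intubation component of the airway-maneuver outcome cannot be counted in the patients for whom the rescue pathway provides it.

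The second ground is not defined by hypoxemia, but it acts within the window in which the primary outcome is observed. It can remove patients who also desaturated, and it takes severe complications out of the comparison between arms.

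**Working it through.** **1. The passages side by side.** Severe hypoxemia with intubation during gastroscopy implies SpO2 below 90%, hence a primary event. Intubation is a listed airway maneuver, hence a secondary event. The same patient meets the third shedding criterion and is excluded. These statements cannot all be followed. LOCF does not resolve the conflict, because hypoxemia during the procedure has no earlier value to carry forward.

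**2. The plan's own sample size.** Inputs from Sample size: 40% vs 20%, 90% power, type I error 0.05 (taken as two-sided), 10% dropout. With unpooled variance:

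n = (1.960 + 1.282)² × (0.40×0.60 + 0.20×0.80) / 0.20² = 10.507 × 0.40 / 0.04 = 105.07 per arm.

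This matches the stated 105, and 105 × 1.1 = 115.5 gives 116 per arm, 232 in total. The figures reproduce.

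**3. Effect of shedding, over an assumed range.** No intubation rate is given, so the shares shed are assumptions. If a share s of an arm with true event rate p is shed, and all those shed are primary events, then

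observed rate = (p − s)/(1 − s), and remaining n = 105 × (1 − s).

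For example, control with s = 5%: (0.40 − 0.05)/0.95 = 36.8%. Intervention with s = 1%: (0.20 − 0.01)/0.99 = 19.2%.

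Power is the exact binomial power of the uncorrected chi-square test, that is, the summed probability of all outcome pairs with a statistic above 3.84. The normal approximation agrees to two decimals.

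| Shed, control / intervention | Observed rates | Difference (points) | Power |
|---|---|---|---|
| none | 40.0% vs 20.0% | 20.0 | 0.89 |
| 1% / 0.5% | 39.4% vs 19.6% | 19.8 | 0.89 |
| 2% / 1% | 38.8% vs 19.2% | 19.6 | 0.88 |
| 2% / 0% | 38.8% vs 20.0% | 18.8 | 0.85 |
| 5% / 1% | 36.8% vs 19.2% | 17.7 | 0.81 |
| 5% / 0% | 36.8% vs 20.0% | 16.8 | 0.77 |
| 5% / 5% | 36.8% vs 15.8% | 21.1 | 0.93 |

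**4. When the direction turns.** The observed rates can be written 1 − 0.6/(1 − c) in control and 1 − 0.8/(1 − t) in intervention, where c and t are the shares shed. The difference is 0.8/(1 − t) − 0.6/(1 − c), which for small shares is about 0.20 + 0.8t − 0.6c. It shrinks when t is below about three quarters of c and widens when t is above that. So the difference can be overstated even when somewhat fewer intervention patients than controls are intubated.

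**The case against.** **Exclusion may not mean exclusion from the analysis.** Withdrawal of consent stands in the same list, so shedding may mean leaving further study procedures. The desaturation will normally have been recorded before the tube is placed, and counting intubation as an airway maneuver fits that reading. Analysis sets are also often left to an analysis plan, which is not shown. This is a fair alternative, and one sentence would confirm it. It does not remove the point: the article states an exclusion from the study, and nowhere says that shed patients' data are kept or counted. The problem is a stated rule that conflicts with the outcome definitions, and not a missing detail.

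**The numbers may be small.** Eligible patients are ASA I or II, aged 18 to 50 and without a known difficult airway, so 5% intubated is an upper scenario with no support in the article. Shedding might also be absorbed by the dropout allowance: if 105 per arm remain, the 5%/1% case gives power 0.82 rather than 0.81. This stands.

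**Stronger readings a reader might infer, which the article does not support:**

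- That the effect of training would be understated. This holds only if controls are shed sufficiently more often; with equal shedding of 5% the difference widens.
- That all of the worst hypoxemia is lost. The third criterion sheds only intubated patients. Those managed by jaw-lift, bag-mask or laryngeal mask stay in unless the second criterion applies.
- That both criteria are defined by the primary outcome. Severe complications need not involve hypoxemia.
- That safety data disappear. The data collection section requires adverse events to be recorded in detail and followed up. What is at risk is their comparison between arms.

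**Conclusion.** The point holds as a conflict in the protocol's wording that, if followed, biases the primary comparison. Patients intubated for severe hypoxemia are excluded after randomisation because of an event that the protocol also defines as its primary outcome and as an airway maneuver. The criterion on severe complications is a second exclusion after randomisation, and it can remove hypoxemia events and between-arm safety comparisons.

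Neither the size nor the direction of the bias can be fixed from the article. Under the assumed shares the observed difference runs from 16.8 to 21.1 points against a planned 20.0, and power from 0.77 to 0.93 against 0.89. With shedding of 1%/0.5% there is almost no change. These figures rest on the planned 40% and 20% rates, on 105 per arm before shedding, and on every shed patient being a primary event. The case for correction does not depend on the larger scenarios: the patients removed are the gravest events, few or many, and an imbalance between arms in either direction would not show in the comparison.

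**What to change.** Reconcile the sections on inclusion and exclusion criteria, Shedding criteria, Primary outcomes and Secondary outcomes by stating that:

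1. the second and third shedding criteria may end further study procedures but do not end inclusion in the analysis;
2. every randomised patient who receives sedation is analysed in the allocated arm;
3. hypoxemia leading to intubation counts as a primary event and as an airway maneuver;
4. severe complications are reported by arm as adverse events.

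The cost is protocol wording. The events are recorded when they happen, and no clinical rule changes. The sample size needs no change on this account, since keeping these patients preserves the planned 40% vs 20% comparison.
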